#### Criteria for discontinuing or modifying allocated interventions {11b}

All participants will be informed that they may stop participating in the HELLO trial at any time and stop completing the questionnaires. However, as the study is fully anonymous we will not be able to remove their data from the global database.

#### Strategies to improve adherence to interventions and data collection

Five elements have been proposed to facilitate adherence to the interventions: (1) detailed communications: Emails and slides have been meticulously prepared to inform the investigators and enable them to inform their teams effectively; (2) centralized materials: all materials are centrally prepared and shipped to the participating ICUs; (3) instructional video: a 3-min video has been created to detail the implementation of the HELLO bundle. Although the video is in English, it uses non-verbal communication to illustrate the different components of the intervention, making it accessible to a wider audience; (4) Maslach Burnout Inventory (MBI): the MBI-HSS questionnaires for healthcare professionals are available in 18 different languages using validated versions provided by Mind Garden (https://www.mindgarden.com/117-maslach-burnout-inventory-mbi); (5) data collection: this study does not include any case report forms (CRFs). No data on patients or family members will be collected. Only the primary and secondary outcomes will be recorded in RedCap.

#### Relevant concomitant care permitted or prohibited during the trial

We have no restrictions on participants receiving other communication, mental health, psychosocial, and any support during our study.

### Outcomes

#### Primary endpoint

The proportion of HCPs with symptoms of burnout will be compared between the interventional and the control cluster. Symptoms of burnout will be measured using the validated version of the 22-item Maslach Burnout Inventory (MBI, Human Services version) [6, 7], which includes three subscales: emotional exhaustion (9 items), depersonalization (5 items), and personal accomplishment (8 items). Each item is scored from 0 (never) to 6 (every day). Respondents with high emotional exhaustion (≥ 27) and/or high depersonalization (≥ 10) scores will be considered to have symptoms of burnout [2].

#### Secondary endpoints

Secondary endpoints include comparing the following between clusters:Emotional exhaustion subscale and the number of HCPs with high emotional exhaustion (score ≥ 27).Depersonalization subscale and the number of HCPs with high depersonalization (score ≥ 10).Loss of accomplishment subscale.Perception of ethical climate (VAS).Satisfaction at work (VAS).Professional conflicts (VAS).Intention to leave the ICU (VAS).Patient-centered care rating (VAS).Family-centered care rating (VAS).Comparison of the proportion of HCPs with symptoms of burnout before and after the intervention in the intervention cluster.

Visual analogue scales (VAS) will be used to assess the intensity of unidimensional measures. Two anchors will be provided: for 0 (no symptom/lowest rating) and 10 (the most intense symptom/highest rating). VASs are convenient, easy, and rapid to administer and have been proven reliable for measuring a characteristic, subjective phenomenon, or attitude that is believed to range across a continuum of values and cannot easily be directly measured.

#### Participant timeline

As shown in Table 4 and Fig. 2, HCPs from both clusters will complete the MBI in September and in November 2024, while the HELLO bundle will be implemented in the interventional clusters between October 14 and November 10. No follow up will be set up for the participating HCPs.

**Table 4 Tab4:** HELLO timeline figure

Timepoint	Study period			
	Enrollment	Pre-intervention	Intervention	Post-intervention
Completion of the ICU characteristics form	X			
Identification of the nurse–physician dyad	X			
Information of the ICU team	X			
Randomization of the ICUs	X			
IRB approval	X			
Approval by the hospital research department	X			
Intervention HELLO bundle (intervention arm) Wait list (control arm)			X X	
Informed consent		X		X
Demographic information		X		X
Assessments Maslach Burnout Inventory (primary endpoint) ¥ 12 additional questions (secondary endpoints) ¥		X X		X X

#### Sample size

Statistical analysis will compare outcomes between intervention and control groups, aiming to demonstrate a reduction in the prevalence of burnout from 39 to 30%, assuming an intra-class coefficient of 0.15, and aiming for a statistical power of 80% (Fig. 3). Intra-class coefficient for the outcome variable was approximated and liberal when compared to precedent cluster trials performed on burnout performed in other context [34].

**Fig. 3 Fig3:**
[figure not shown]
Sample size estimation assuming 50 respondents per cluster, a reduction in the prevalence of burnout from 39 to 30%, assuming an intra-class coefficient of 0.15 (base intra-class coefficient, range 0.1–0.2)

Primary and secondary analyses will be performed at an individual level adjusting for clustering. No imputation will be performed for missing variables.

Subgroup analyses will be conducted to explore potential moderators of intervention effectiveness.

Assuming an intra-class correlation of 0.15, 146 centers and 50 respondents per center, the study would allow to demonstrate a reduction in burnout prevalence from 39 to 30% with a statistical power of 80%. This study will enroll at least *k* = 73 clusters of 50 participants in average, totaling approximately *n* = 7300 participants (assuming an average cluster size of *m* = 50). The sample size was determined by power calculations from previous cross sectional studies [3, 7, 35, 36]. Based on estimated effect sizes, ICCs, and SDs of the outcome in the population from previous data, and accounting for attrition related to failure to obtain IRB or local research committees approval, we estimated that at least *k* = 73 clusters and *n* = 7300 participants would be sufficient to detect significant effects with 80% power in the primary outcome. However, because there was an uncertainty about the proportion of IRB and local research committees’ failure, as well as the number of ICUs finally not willing to participate to the trial, we included all the 434 ICUs (217 per group) who applied to the IRB before July 1st, 2024.

#### Assignment of interventions: allocation

Sequence generation: Cluster randomization matched on the ICU size and country has been performed using cvrand package in R.

Concealment mechanism: Randomization did not occur before IRB could be obtained in every center. However, as we randomized 217 clusters for a target of “at least” 73 clusters, all matched clusters have been randomized together—which ensures allocation concealment is maintained, limiting selection bias.

Implementation: Cluster were randomized to treatment or control within each strata with a 1:1 allocation ratio.

Assignment of interventions: blinding: Blinding for the HELLO trial is not possible.

### Statistical methods

#### Primary and secondary outcomes

Data will be described as median and interquartile range (IQR) or number and percentage. Categorical variables will be compared using Fisher's exact test and continuous variables using the nonparametric Wilcoxon test, Mann–Whitney test, or Kruskal–Wallis test.

The primary method of analysis will be a generalized linear mixed-effects model, which will be adjusted for cluster. We will use an intention-to-treat approach with a binary exposure variable indicating if the participant was randomized to the intervention or control group.

Predefined subgroup analyses will include:Center and country effect as assessed using mixed effect model. Briefly, we will assessed effect of the intervention while accounting for center and country effect. Center and country will be examined in dedicated mixed effect model and will be added as random effect on the intercept. Impact of the intervention will be reported when adjusted for these confounders. Center and country effect will be reported [37]. To test for the significance of center and country effects on outcome, we will use permutation tests [38]. Difference in rate of burnout will across centers and countries will be reported as median odds-ratio with their confidence interval. Influence of centers and country will be plotted.In addition, influence of adherence to protocol will be assessed. Impact of adherence on outcome will be reported by quartile of adherence.Last, influence of the job of respondents will be assessed.

If any additional exploratory or sensitivity analyses should be performed, they will be reported in the manuscript as post hoc analyses and interpreted as exploratory hypothesis generating analyses.

We will use an appropriate bootstrapping method with an identity link. We will use two-tailed tests for all models with statistical significance thresholds of 0.05. Results will be reported as mean difference, incidence rate ratio or odds ratios as appropriate.

Statistical analyses will be performed with R statistical software, version 3.4.3 (available online at http://www.r-project.org/) and packages ‘lme4’,and’lmerTest’. A *p* value < 0.05 will be considered significant.

Results will be reported in adherence with standards for reporting implementation studies of complex interventions guidelines [39].

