#### Modalities of informed consent

Healthcare professionals (HCPs) participating in this trial must agree to be part of the study and consent to having their data published once they log into the REDCap file, which will collect the Maslach Burnout Inventory (MBI), secondary outcomes, and demographic data. Additionally, some countries may require individual informed consent to be signed by each HCP prior to trial participation.

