### Confidentiality

Participants will not provide any identifying information (such as full names). Therefore, we will not collect any identifying information beyond what is sufficient for a unique ID (in addition to age and gender of the respondent).

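### The stated primary model holds only arm and cluster, so a systematic arm difference in who answers the survey would pass unadjusted into the burnout contrast, although age, gender and (by implication) job are collected

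*Protocol article*

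**What the plan says.** The primary model is described twice in the protocol article. Under Statistical methods: "The primary method of analysis will be a generalized linear mixed-effects model, which will be adjusted for cluster", followed by "We will use an intention-to-treat approach with a binary exposure variable indicating if the participant was randomized to the intervention or control group". Under Sample size: "Primary and secondary analyses will be performed at an individual level adjusting for clustering". Neither place names a respondent characteristic.

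The characteristics are nevertheless available. Modalities of informed consent describes a REDCap file "which will collect the Maslach Burnout Inventory (MBI), secondary outcomes, and demographic data". Table 4 schedules demographic information at both the pre- and the post-intervention survey. Confidentiality says that only enough for a unique ID is collected, "in addition to age and gender of the respondent". Job is not listed as a data item, but the predefined subgroup analyses end with "Last, influence of the job of respondents will be assessed", which presupposes it.

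The same list contains a model with centre and country as random intercepts, in which the intervention effect is reported after adjustment for them. No analysis adjusting for age or gender is stated.

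**The concern.** The primary outcome is the proportion with burnout among those who complete the post-intervention survey. Allocation is made at ICU level and is not blinded. Individuals enter later by clicking a survey link and ticking consent (Ethics section), and they may stop completing questionnaires at any time. Randomising ICUs balances the ICUs in expectation; it does not balance the people who choose to answer if the choice depends on arm.

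Such dependence is conceivable. In intervention ICUs the local nurse–physician dyad forwards messages and visits at least twice a week, and control ICUs have none of this during the period. If one staff group responds more readily in one arm, and that group has a different burnout rate, the difference enters the arm contrast. A random ICU intercept does not absorb it, because each ICU belongs to one arm and an arm-level shift is what the arm coefficient estimates.

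The plan also labels any further sensitivity analysis as post hoc and exploratory. An adjusted analysis added after the data are seen would therefore lose confirmatory standing under the plan's own rule.

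**Working it through.** **1. The plan's own figure.** Inputs from Sample size and Statistical methods: 39% versus 30%, ICC 0.15, 50 respondents per ICU, two-sided 0.05, 80% power.
- Individually randomised size (pooled variance): 437 per arm.
- Design effect: 1 + (50 − 1) × 0.15 = 8.35.
- 437 × 8.35 = 3,649 per arm; 3,649 / 50 = 73.0 ICUs per arm, or 146 in total.

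The stated 146 centres and 80% power reproduce, with no covariate adjustment built in.

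**2. Size of a mix effect.** The documents give neither burnout rates by job nor an expected imbalance, so both are assumptions.
- Spurious difference = burnout gap between groups × arm difference in mix.
- Standard error under no effect, at 39% and 73 ICUs per arm: √(2 × 0.39 × 0.61 × 8.35 / 3,650) = 0.0330.
- Two-sided error with bias b: Φ(−1.96 + b/SE) + Φ(−1.96 − b/SE).

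| Gap (points) | Mix difference (points) | Bias (points) | Share of 9-point target | Two-sided error, 73 ICUs per arm |
|---|---|---|---|---|
| 5 | 5 | 0.25 | 3% | 5.1% |
| 10 | 5 | 0.50 | 6% | 5.3% |
| 10 | 10 | 1.00 | 11% | 6.1% |
| 15 | 10 | 1.50 | 17% | 7.4% |
| 15 | 15 | 2.25 | 25% | 10.5% |

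For the central row, b/SE = 0.010 / 0.0330 = 0.303. This is a normal approximation on the risk-difference scale, not a fit of the mixed model.

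**3. Could chance alone produce a 10-point mix difference?** Assume the share of one job group varies between ICUs with SD 0.15. The chance SD of the arm difference at 73 per arm is 0.15 × √(2/73) = 0.025, or 2.5 points. A 10-point difference is about 4 such SDs, so it needs systematic differential response.

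**4. Precision.** The variance of an ICU mean is proportional to 0.15 + 0.85/50 = 0.167, of which the within-ICU part is 0.017, or 10.2%.
- If the covariates act only within ICUs and explain 2%, 5%, 10% or 20% of that part, power moves from 80.0% to 80.1%, 80.2%, 80.4% or 80.8%.
- A larger gain needs them to explain between-ICU variance, which is 0.15 × 0.39 × 0.61 = 0.0357. With a 10-point job gap, explaining 5% needs an ICU-to-ICU SD in job mix of √(0.05 × 0.0357) / 0.10 = 0.42. Explaining 15% needs √(0.15 × 0.0357) / 0.10 = 0.73, although the SD of a proportion cannot exceed 0.5.
- With the assumed mix SD of 0.15, job explains (0.10 × 0.15)² / 0.0357 = 0.6% of between-ICU variance for a 10-point gap and (0.15 × 0.15)² / 0.0357 = 1.4% for a 15-point gap. Explaining 5% would lift power only to 81.8%, so these values are worth well under 1 point.

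**The case against.** The strongest reply is that this is a condensed article, that covariate lists belong in a statistical analysis plan, and that adjusting for cluster does not mean adjusting for nothing else. A cluster-adjusted mixed model with an intention-to-treat arm term is a valid primary analysis. This stands in part: a fuller plan may list covariates, and the point is limited to the model as stated. But the article does describe the primary model, twice and consistently, and it places job in a separate item. That is a stated choice open to comment.

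Second, nothing in the document shows differential response; both arms complete the same surveys at the same times. Chance imbalance is already reflected in the standard error and is not bias. This stands, and it makes the size conditional.

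Third, job is examined in a predefined analysis. That is true, but assessing its influence under a subgroup heading does not commit the plan to an intervention effect adjusted for respondent mix, and age and gender appear in no stated analysis. The centre and country model adjusts for place, not person.

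Three stronger readings are tempting and are not supported:
- A reader might infer that leaving these covariates out wastes material precision. Step 4 of the working shows otherwise: about 90% of the contrast variance lies between ICUs.
- A reader might take the error rate at 217 ICUs per arm (8.2% for a 1.0-point bias) as the likely one. It requires every randomised ICU to take part, whereas the article expects losses at ethics approval.
- A reader might conclude from "Only the primary and secondary outcomes will be recorded in RedCap" that job and demographics will not be recorded. In context the sentence sits beside the absence of case report forms and of patient or family data, and the consent section, Table 4 and Confidentiality all provide for demographics. It is loose wording.

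**Conclusion.** The point holds as a bias safeguard. The stated primary model leaves out respondent characteristics that the trial collects, in a design where randomisation does not secure the respondent mix. If response differs systematically between arms, the primary contrast carries the difference unadjusted: 1.0 point, or 11% of the target effect, with about 6.1% two-sided error at 73 ICUs per arm, for an assumed 10-point gap and 10-point imbalance. At 5 points each the effect is negligible; at 15 points each it is 2.25 points and 10.5%. All gaps and imbalances are assumptions, and the documents do not show that such an imbalance will occur.

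Adjustment deals only with measured traits. It does not correct response driven by burnout itself or by enthusiasm for the bundle.

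**What to change.** Prespecify job category (nurse, physician, other), age group and gender as fixed effects in the primary mixed model. Give each a 'not stated' level, so that nobody is dropped under the no-imputation rule; age therefore has to be grouped. A four-week greeting campaign cannot plausibly alter these traits, so using values reported in November carries little risk.

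Keep the arm-and-cluster model as a named sensitivity analysis. Tabulate respondent mix by arm and survey wave, so that readers can see whether adjustment mattered.

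As a minor correction, amend the RedCap sentence under Strategies to improve adherence to interventions and data collection to say that job and demographics are also recorded.

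The cost is wording only, since the analyses already planned presuppose these data. The downside is a few more parameters and an odds ratio that is conditional on these covariates.

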#### Intervention description

Intervention clusters will implement the HELLO bundle for four weeks, starting Monday, October 14, 2024. Twenty posters will be displayed in various locations within the ICU, including workstations, dressing rooms, and toilets. These posters, designed by the ESICM steering committee, will be shipped to all participating centers in either August (for the intervention group) or January (for the control, waitlist centers). The blue posters feature the term "HELLO" in different languages, the HELLO logo with a smiley face for the letter "O", and the ESICM logo.

Every Monday and Friday during the four-week intervention, the study's ESICM coordinators will send emails to the HELLO dyad at each participating center, highlighting the impact of positive psychology, team cohesion, and communication on healthcare professionals' (HCPs) well-being. These emails will then be forwarded to all HCPs via email, WhatsApp, or any other channel, and may also be displayed in the ICU by the local dyad. Saying "HELLO" before any huddles, handovers, or staff meetings will be encouraged.

Two HELLO jars/boxes will be placed in the ICU, designed by ESICM and sent to the centers. HCPs will be invited to write and insert positive messages about their colleagues and their work experience in the ICU into these jars/boxes. These messages will be accessible to anyone in the ICU who wishes to read them. At least twice a week, the HELLO dyad (or the head nurse and the department chief) will visit the ICU to greet everyone, set an example, explain the study, and share their reasons for participating in the trial.

Lastly, two paperboards will be displayed and updated as needed. These boards can include direct messages, stickers, drawings, photos, or any positive notes directed to other HCPs or the entire ICU.

In the ICUs from the intervention cluster, ESICM officers will make contact once a week to assess a rough estimate of the intervention's dosage. Each of the six components will be scored from 0 to 4, as illustrated in Table 3.

**Table 3 Tab3:** Adhesion score to measure the rate of implementation of the HELLO intervention

Adhesion score	0	1	2	3	4	+ 1
Number of Hello posters displayed (over 4 weeks)	None	< 5	5–10	10–15	> 15	More poster printed and displayed
Email reminders	Never forwarded	Forwarded only one week	Forwarded only two weeks	Forwarded only three weeks	Forwarded all the four weeks	Emails printed and displayed in the ICU

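### Two of the predefined subgroup analyses, adherence quartiles and centre/country random intercepts, cannot show what moderates the bundle's effect, and the adherence score in Table 3 cannot be assigned consistently

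*Protocol article*

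**What the plan says.** In the protocol article, the text after Figure 3 in the Sample size section sets the aim: "Subgroup analyses will be conducted to explore potential moderators of intervention effectiveness". Under Statistical methods, Primary and secondary outcomes, three predefined subgroup analyses follow.

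- **Centre and country.** "Center and country will be examined in dedicated mixed effect model and will be added as random effect on the intercept". They are described as confounders to adjust for. Their effects on the outcome are tested by permutation, and differences in burnout rate are summarised as median odds ratios.
- **Adherence.** "Impact of adherence on outcome will be reported by quartile of adherence". No comparator and no adjustment are given.
- **Job.** "Last, influence of the job of respondents will be assessed". No method is given.

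The same section says that any further exploratory analysis will be reported as post hoc.

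The Intervention description limits adherence scoring to ICUs in the intervention arm, through weekly contacts during the four weeks. On the score it says: "Each of the six components will be scored from 0 to 4, as illustrated in Table 3". Table 3 then has columns 0, 1, 2, 3, 4 and a sixth headed + 1.

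**The concern.** A moderator analysis asks whether the difference between arms varies with some factor. That needs the factor to be defined in both arms and a term that lets the arm effect vary with it.

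Adherence exists in one arm only and arises after randomisation. Three of the six components (huddle greetings, jar messages, board messages) record what staff chose to do. An ICU with a good climate may plausibly have both more of this behaviour and less burnout, whether or not the bundle works. A gradient across quartiles could then be read as dose-response.

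A random intercept for country lets the burnout level differ between countries but holds the arm effect constant. It cannot answer the question the Sample size section asks. Because unlisted analyses become post hoc, an interaction not named now loses its predefined status.

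The adherence analysis also depends on a score that two assessors could assign differently from the same facts.

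**Working it through.** **1. The plan's own figure.** Inputs from the Sample size section: "Assuming an intra-class correlation of 0.15, 146 centers and 50 respondents per center", for "a reduction in burnout prevalence from 39 to 30% with a statistical power of 80" percent. Statistical methods adds: "We will use two-tailed tests for all models with statistical significance thresholds of 0.05".

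- Respondents per arm without clustering: [1.96 × √(2 × 0.345 × 0.655) + 0.842 × √(0.39 × 0.61 + 0.30 × 0.70)]² / 0.09² = 437.
- Design effect: 1 + 49 × 0.15 = 8.35.
- Clusters per arm: 437 × 8.35 / 50 = 72.98, so 73 per arm and 146 in total. The figure reproduces. The 9-point difference is the yardstick below.

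**2. Adherence gap with zero true effect.** Assumption, not in the documents: correlation r between a better ICU climate (lower underlying burnout) and adherence.

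- Between-ICU SD of prevalence, taking the ICC on the prevalence scale: √(0.15 × 0.39 × 0.61) = 0.189.
- Mean of a standard normal in its top quartile: φ(0.674) / 0.25 = 1.271.
- Expected gap between extreme quartiles: 2 × 1.271 × 0.189 × r = 0.480 r.

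| r | Gap, prevalence-scale ICC | Lowest vs highest adherence quartile, latent-scale ICC (simulated, 73 ICUs) |
|---|---|---|
| 0 | 0 | 39% vs 39% |
| 0.1 | 4.8 points | not run |
| 0.2 | 9.6 points | 43% vs 35% (8 points) |
| 0.3 | 14.4 points | 45% vs 33% (12 points) |

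**3. Sampling error of the gap.** Variance of one ICU's observed prevalence: 0.39 × 0.61 × 8.35 / 50 = 0.0397.

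- 73 intervention ICUs, 18.25 per quartile: √(2 × 0.0397 / 18.25) = 0.066, so 1.96 SE is about 12.9 points.
- 217 intervention ICUs, 54.25 per quartile: √(2 × 0.0397 / 54.25) = 0.038, so 1.96 SE is about 7.5 points.

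On the prevalence scale, only the expected gap at r = 0.3 exceeds 1.96 SE with 73 ICUs. With 217, those at 0.2 and 0.3 do.

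**4. Arm effect without an interaction.** Two equal strata were simulated. Arm effects of −18 and 0 points average to −8.9. Effects of −9 in both average to −9.0. The overall effect does not separate the two cases. The between-stratum contrast does (−17.9 against about 0).

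**5. Power of an interaction.** Assumptions: two equal cluster-level subgroups, 50 respondents per ICU, ICC 0.15.

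- 73 clusters per arm (36.5 per cell): SE = √{2 × (0.2379 + 0.21) × 8.35 / (36.5 × 50)} = 0.064. Power is about 29% for a 9-point difference in effects and about 80% for 18 points.
- 217 clusters per arm: SE = 0.037. Power for 9 points is about 68%.

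**6. Table 2.** Of 67 countries listed, 45 have four or fewer randomised sites and 17 have one, before losses to ethics approval.

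**7. Table 3.**

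- Ten posters scores 2 or 3.
- In the jar and board rows, 10 messages scores 1 or 2, 20 scores 2 or 3, and 30 scores 3 or 4.
- More than 50 messages appears only in the + 1 column, so it has no score on the 0 to 4 scale.
- The maximum is 6 × 4 = 24, or 6 × 5 = 30 if the extra column counts.

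**The case against.** The best defence is that these analyses are secondary, the primary analysis is by intention to treat, and the article calls the adherence score only a rough estimate of dosage. It never claims dose-response. Three of the six components (posters, email forwarding, leading by example) depend mainly on the local dyad rather than on the mood of the staff. The documents give no correlation between climate and adherence, and the article itself describes the ICC as approximate. All of this stands, so the gap in the working is a range under assumptions. It does not remove the problem that a causal term is attached to a one-arm, unadjusted comparison.

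A reader might infer that none of the predefined subgroup analyses can find a moderator. The documents do not support that. Job is listed and is observed in both arms; only its model term is unstated, which an article may leave to the analysis plan.

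A reader might also fault the missing centre-by-arm interaction. Each ICU is in one arm, so that interaction cannot be estimated, and a random intercept is the right description for centre.

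Adjusting for country is legitimate too. The difficulty is presenting it as a subgroup analysis under a moderator aim. A country-level random slope would be poorly supported, given how many countries have very few sites.

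The Table 3 defects are largely editorial: a boundary case moves one component by one point. They matter because quartile membership is built on that score.

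**Conclusion.** The point holds for adherence and for country. Burnout by adherence quartile is an observational contrast within the intervention arm. With no effect at all, it could show an expected gap of about 5 to 14 points for correlations of 0.1 to 0.3, if the ICC of 0.15 applies on the prevalence scale, or about 8 and 12 points at 0.2 and 0.3 on a latent scale. Those correlations are assumptions, and with 73 intervention ICUs sampling error is large enough that smaller gaps would often not stand out. It does not follow that a spurious gradient will appear or be published as dose-response, only that the planned analysis could not distinguish one from a real effect.

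The country random intercept describes prevalence and leaves effect moderation unexamined. The Table 3 inconsistencies are visible on the page and need no assumption. This should be corrected before analysis, but it does not bear on the primary comparison.

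**What to change.** 1. **Adherence.** Label the analysis exploratory and non-randomised, and drop the causal term. Regress November burnout on the continuous ICU adherence score, adjusted for the ICU's September burnout and its size. Both are already collected, through the pre-intervention survey and the ICU characteristics form. Adjustment reduces confounding but does not remove it. Using randomisation as an instrument with control adherence set to zero is not recommended as a routine repair: control ICUs are not scored and other support is unrestricted, so it adds untested assumptions.
2. **Moderators.** Predefine an exploratory arm-by-region interaction, with very small regions merged in advance (Oceania has 2 sites), and state that job will be tested as an arm-by-job interaction. Present the centre and country random intercepts as variation in prevalence, not as subgroup analyses of the effect.
3. **Table 3.** Make the bands mutually exclusive, and state whether each component runs 0 to 4 or 0 to 5 (maximum 24 or 30) and how more than 50 messages is scored.

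The cost is a few sentences, a corrected table and a small amount of extra analysis, with no new data. The interaction tests have low power and stay exploratory.

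### The 0.05 rule covers every model, so any secondary comparison can be declared significant even if the primary comparison fails

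*Protocol article*

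**What the plan says.** In the protocol article, Statistical methods, under Primary and secondary outcomes, the decision rule is: "We will use two-tailed tests for all models with statistical significance thresholds of 0.05". The same subsection ends by repeating that a p "value < 0.05 will be considered significant". Neither sentence separates the primary endpoint from the secondary ones. The Sample size section shows that the secondary analyses fall under this rule: "Primary and secondary analyses will be performed at an individual level adjusting for clustering".

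The article also addresses interpretive status, but only for analyses beyond those listed: "they will be reported in the manuscript as post hoc analyses and interpreted as exploratory hypothesis generating analyses".

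The list of secondary endpoints opens with "Secondary endpoints include comparing the following between clusters". Two of its entries name both a score and a count above a cut-off: "Emotional exhaustion subscale and the number of HCPs with high emotional exhaustion (score ≥ 27") and "Depersonalization subscale and the number of HCPs with high depersonalization (score ≥ 10"). The accomplishment subscale, six VAS ratings and a before/after comparison within the intervention arm follow. The Abstract and the Objectives give a shorter list of nine between-arm outcomes, with counts only for the three MBI subscales.

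**The concern.** The plan names one primary contrast: burnout symptoms after the intervention, intervention against control. That test is in order. The difficulty is that the same declaration of significance is attached to every other model. The article states no order of testing, no condition on the primary result and no adjustment. The only cautionary label it gives is reserved for unplanned additions.

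Under this rule a trial that misses its primary endpoint could still report a significant gain on, say, satisfaction at work or intention to leave. The Expected outcomes section cites literature pointing to improvement in both areas, so an isolated result there could easily be given too much weight. At stake is how often a bundle with no effect would produce at least one such result.

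**Working it through.** **Step 1. The plan's own figure, to confirm the alpha in use.** Inputs from Sample size and Trial design: 39% against 30%, intra-class correlation 0.15, 50 respondents per center, 80% power, 1:1 allocation. From Statistical methods: two-sided 0.05.

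- Per arm without clustering: n = [1.960·√(2·0.345·0.655) + 0.842·√(0.39·0.61 + 0.30·0.70)]² / 0.09² = 437 (rounded up).
- Design effect: 1 + (50 − 1)·0.15 = 8.35.
- Clusters per arm: 437·8.35/50 = 72.98, so 73 per arm and 146 in total. Power at 73 per arm is 80.0%.

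The stated 146 centers reproduce at two-sided 0.05, so the primary test has no conflict of alpha or sidedness.

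**Step 2. Count the comparisons.** Under Secondary endpoints: emotional exhaustion (score and count) 2, depersonalization (score and count) 2, accomplishment 1, VAS ratings 6. Total: 2 + 2 + 1 + 6 = 11 between-arm comparisons. The before/after comparison would be a twelfth, but it is within one arm and is left out. The Abstract and the Objectives give 9.

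**Step 3. Chance of at least one false positive when all nulls are true.** Each test is taken to have its nominal size: 0.05 in either direction, 0.025 in the direction of benefit. With independent tests:

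- 11 tests: 1 − 0.95¹¹ = 43.1% in either direction; 1 − 0.975¹¹ = 24.3% for benefit.
- 9 tests: 1 − 0.95⁹ = 37.0% in either direction; 1 − 0.975⁹ = 20.4% for benefit.

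The endpoints come from the same respondents and will be correlated, but the document gives no correlations. The table therefore assumes a common correlation between the test statistics (multivariate normal, 1,000,000 simulated draws; the first row is exact).

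| Assumed correlation | 11 tests, either direction | 11 tests, benefit | 9 tests, either direction | 9 tests, benefit |
|---|---|---|---|---|
| 0 | 43.1% | 24.3% | 37.0% | 20.4% |
| 0.3 | 37.5% | 19.1% | 32.6% | 16.5% |
| 0.5 | 30.3% | 15.1% | 27.0% | 13.5% |
| 0.7 | 22.2% | 11.1% | 20.2% | 10.1% |
| 0.8 | 18.0% | 9.0% | 16.6% | 8.3% |

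Setting each score/count pair at 0.8 and all other pairs at 0.5 changes little: 29.4% in either direction and 14.7% for benefit with 11 tests.

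**Step 4. Bound and expected counts.** Under any dependence, the chance of at least one false benefit among 11 tests cannot exceed 11 × 0.025 = 27.5%. The expected number of false significant results is 11 × 0.05 = 0.55, of which 11 × 0.025 = 0.275 are apparent benefits.

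**Step 5. Effect of an adjustment.** Holm across the 11 starts at 0.05/11 = 0.0045 and keeps the family-wise error at or below 5% under any dependence. It is about 3.7% in simulation with the 0.5/0.8 structure of Step 3.

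**The case against.** The strongest reply is that this is a condensed journal article, that multiplicity for secondary endpoints is commonly left to the analysis plan, and that unadjusted secondaries after a single primary are a matter of interpretation. Much of this is fair. An analysis plan that is not shown may order, gate or label the secondaries. The point therefore cannot be that the trial lacks a multiplicity strategy; a reader might infer that, but the article alone does not show it. What remains is that the article does more than stay silent. It fixes a rule for every model and confines the hypothesis-generating label to additional analyses, so a later gate or label would have to change that published rule.

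It is also fair that nothing in the article calls the secondaries confirmatory. They stand in their own list, power is claimed only for the primary outcome, and subgroups are introduced as exploration of possible moderators. A reader might infer confirmatory status from the placement of the exploratory label, but the text does not say so. It says only that they may be called significant.

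The count is open to reading as well. Eleven comes from treating the two score-and-count entries as two tests each, while the shorter lists give nine. High emotional exhaustion and high depersonalization also make up the primary definition, so they partly break down the primary result. The nine-test columns show that the conclusion does not depend on the choice.

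**Conclusion.** The point stands at modest severity. Followed as written, the rule lets each secondary comparison be declared significant whatever the primary shows. With 11 true nulls, the chance of at least one significant difference is about 18–43% in either direction and about 9–24% for a benefit. With nine it is about 17–37% and 8–20%. These ranges rest on assumed common correlations of 0.8 down to 0 and on each test having its nominal size. Even at 0.8 with 11 tests, both rates are about 3.6 times the per-test level (18.0/5 and 9.0/2.5).

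A reader might infer a chance of about 30% of a false significant benefit. That is not supported: about 30% is the either-direction figure at an assumed correlation of 0.5, and the benefit figure there is about 15% and can never exceed 27.5%. A reader might also infer that the primary result is compromised. It is not: there is one primary endpoint, and its alpha and power are unaffected.

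**What to change.** Amend the statistical methods so that the p < 0.05 decision rule applies to the primary comparison only. Label the secondary endpoints and the predefined subgroups as supportive or exploratory, reported as effect estimates with 95% confidence intervals and no claim of significance.

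If the sponsor wants confirmatory secondary claims, test the between-arm secondaries only after a significant primary, with Holm across them, and keep the before/after comparison and the subgroups exploratory. This option needs one agreed list, because Holm's divisor depends on whether the family has nine or 11 members.

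Either option takes a few sentences and needs no further data or participants. The cost is that some secondary results with p just below 0.05 could no longer be called significant. If the analysis plan already contains such a rule, the article's wording should be aligned with it.
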